### Intervention protocol

#### Physician-pharmacist collaborative diabetes clinics

Three physician-pharmacist collaborative diabetes clinics will be established after the pharmacists get comprehensive training. Pharmacists in the collaborative clinics will provide several services which mainly consist of four aspects, including diabetes education, medication guidance, lifestyle intervention, and identification and treatment of adverse drug reaction and complications, as shown in Table 2.

Three measures will be taken to make sure that the project will be carried out smoothly in the collaborative clinics. 1) In the first week, a pharmacist from the Second Xiangya Hospital will stay in the collaborative clinic, monitor the trained local pharmacist and data collector’s work, and give him/her guidance to run the collaborative clinic well. 2) A pharmacist from the Second Xiangya Hospital will periodically go to the primary hospitals and check the progress of the project. Every week, there will be an internet meeting consisting of the PI, main participants and the pharmacists from the intervention group to report the process of the project, describe the problems they meet and exchange their experience in the collaborative clinics. 3) Data collectors are required to entry and upload the electronic CRF forms to the Second Xiangya Hospital within two days when they have finished the printed forms. A separate research staff will carefully check the data and immediately inform the data collectors to amend the errors once occur.

#### Usual care clinics

Similar to physicians in the collaborative clinics, physicians in the usual care clinics will provide routine services, mainly including diagnosis and treatment without education due to limited time. No pharmacists will be involved in the control group. Data collectors will present in the clinic to enroll patients and collect data of the assessments the same as in the collaborative clinics.

In order to ensure the implementation of the project in the usual care clinics, three measures will be taken: 1) In the first week, a pharmacist from the Second Xiangya Hospital will stay in the clinic and monitor the data collector’s work. A participant from the Second Xiangya Hospital will periodically go to the primary hospitals and check the progress of the project. 2) Every two weeks, an internet meeting consisting of the PI, main participants and the data collectors will be held to monitor the process of the project. 3) Same as the intervention group, data collectors are required to entry and upload the electronic CRF forms to the Second Xiangya Hospital within two days.

#### Follow-up visits and data collection

All the patients in either the intervention group or in the control group are required to visit their corresponding clinic at the 3rd, 6th, 9th and 12th month. They are allowed to arrive at the clinic within seven days before or after the appointed day. The measurement domains required to collect, survey methods and collection time-points are listed in Table 3.

**Table 3 Tab3:** Measurement domains, survey methods and collection time-points

Variable	Component	Measurement methods	Baseline	3rd M	6th M	9th M	12th M
**Socio-demographic parameters**	Gender, age, telephone, address, education, occupation and annual income	Face-to-face interview	√				
**Clinical parameters**	Height, weight, waist to hip ratio, fasting blood glucose, 2-h postprandial blood glucose, HbA1c, diabetes complications, blood pressure and lipid files	Face-to-face interview, telephone or online interview	√	√	√	√	√
**Behavior parameters**	Medication adherence, diabetes’ knowledge, lifestyle, diabetes treatment target and treatment behavior		√ √	√	√	√	√ √
	Treatment satisfaction						√
**Economic parameters**	Direct costs (Average daily Medicine, outpatient clinic visit fees, and hospitalization fees if occurs), Indirect costs (deducted income due to absence of working, traffic and accommodation fees)	Face-to-face interview, telephone or online interview	√	√	√	√	√

In order to enhance patients’ follow-up rate, two measures will be taken: 1) The trained data collectors will send a text message to remind the patient three days before the appointed follow-up day. If the patient has not shown up in the clinic one day after the appointed follow-up day, they will call the patient. If the patient still insists not coming, the reasons will be recorded in the CRF form. 2) All the patients from either the control group or the intervention group will receive free tests of fasting blood glucose (FBS), 2-h postprandial blood glucose (2hPBG) and HbA1c at the 3rd, 6th, 9th and 12th month to sustain their involvement in the study.

### Outcomes

#### Primary outcomes measure

The primary outcome measure is glucose control (including fasting blood glucose, 2-h postprandial blood glucose and HbA1c) at 12 months’ follow-up adjusted for baseline value.

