### Data analyses

The sample size was calculated by using the PowerSampleSize program (Vanderbilt University). The data will be analyzed using the SPSS software package (Statistical Package for the Social Sciences), version 22.0 for Windows (SPSS Inc., Chicago, Illinois, USA). Data will be checked for normal distribution by means of the Kolmogorov–Smirnov's test. Values are presented as mean ± standard deviation or median (range) for parametrically or nonparametrically distributed variables, respectively. In compliance with the distribution of data, Student's t-test or Mann–Whitney's U-test will be used for comparisons between the two groups. Chi-square or Fisher's exact tests will be used to compare between the groups with respect to categorical data. The follow-up assessment data will be analyzed using Generalized Linear Mixed Model and survival analysis. *P* < 0.05 is considered statistically significant. All tests are two tailed.

For cost-effectiveness analysis, we will collect the direct and indirect costs of each enrolled patient with T2DM, evaluate their quality of life through EQ-5D-3L utility value from data provided by patients, calculate quality-adjusted life years (QALYs), and analyze the effects of multiple variables by the Linear Mixed Effects Model. Based on this model, the differences between the average costs and the results will be analyzed during the 12 months. The incremental cost effectiveness (ICER) will be calculated, and the univariate and multivariate analyses will be performed.

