### Sample size determination

Sample size is calculated using a two-tailed test and indicated that to detect an absolute difference of 0.76% in HbA1c in favor of the intervention group with α = 0.05, β = 0.1 (90% power), and standard deviation of 1.0%, a sample size of 36 patients per group was required [18]. An additional 10% was added to allow for patients dropping out of the study, making a target sample size of at least 40 patients in each primary hospital, same as a previous study [19]. Our target enrolled patient number in each hospital is 100, and we plan to complete patient recruitment in 6 months. If the eligible patients have reached 100 in less than 6 months, we will continue the enrollment until the end of the sixth month. If the enrolled patients have not reached our target number at the end of the sixth month, we will continue to enroll patients for an extra month and then stop. We estimate that the final included patient number is around 80 to 120 in each primary hospital.

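### The primary outcome names three glucose measures without a deciding measure or success rule, so the stated 5% error rate and 90% power fit the primary claim only if HbA1c decides

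*Protocol article*

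**What the plan says.** Three sections of the protocol article bear on the point.

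- **Primary outcomes measure.** The definition reads: "The primary outcome measure is glucose control (including fasting blood glucose, 2-h postprandial blood glucose and HbA1c". The time point is month 12, and the comparison takes the baseline value into account. One outcome is named, and three laboratory measurements are listed under it. None is singled out, and no rule combines them.
- **Data analyses.** A P value below 0.05 "is considered statistically significant. All tests are two tailed". This criterion is given once, for all analyses.
- **Sample size determination.** The trial is sized "to detect an absolute difference of 0.76% in HbA1c in favor of the intervention group". The other inputs are a two-sided alpha of 0.05, 90% power and an SD of 1.0%, and the result is that "a sample size of 36 patients per group was required". Neither fasting nor 2-hour postprandial glucose enters the calculation, and no target difference or standard deviation is given for them.

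**The concern.** A primary outcome has to tell the reader, before any data are seen, what result will count as success. Here three results could come out differently, for instance a lower fasting glucose with no difference in HbA1c, and the article does not say how that would be read.

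Two things are at stake. First, if the choice stays open until the results are known, the chance of a false claim of better glucose control can exceed the 5% that the article states. Second, the alpha and power in the sample size section belong to a single HbA1c test. They carry over to the primary claim only if HbA1c decides it. The Abstract links a positive result to use of these clinics in primary hospitals across China and to diabetes care policy, so the meaning of a positive result should be settled in advance.

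**Working it through.** **1. The plan's own figure.** Inputs from Sample size determination: difference 0.76, SD 1.0, two-sided alpha 0.05, power 90%.

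n per group = 2 × [(1.960 + 1.282) × 1.0 / 0.76]² = 36.38, which rounds up to 37. The article states 36, a difference of one patient with no practical effect. Adding 10% for dropout gives 36 / 0.9 = 40, as stated. The 5% and 90% are therefore the properties of one comparison on HbA1c.

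**2. Any one of the three is enough.** Assume no true effect on any measure, a valid 5% two-sided test for each, and a common pairwise correlation r between the three test statistics. The article gives no r, so a range is shown.

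- Independent: 1 − 0.95³ = 0.143.
- Correlated: P(at least one |Z| > 1.96) for three equicorrelated standard normals, from 4 million simulated draws.

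| Assumed r | Any of three, two-sided | Any of three, favourable direction only |
|---|---|---|
| 0 | 14.3% | 7.3% |
| 0.5 | 12.5% | 6.3% |
| 0.7 | 10.9% | 5.5% |
| 0.8 | 9.8% | 4.9% |
| 0.9 | 8.4% | 4.2% |
| 0.95 | 7.3% | 3.7% |

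The nominal values are 5% and 2.5%. Over this range the two-sided rate is about 1.5 times (7.3 / 5) to 2.9 times (14.3 / 5) nominal. It falls to 5% only at r = 1.

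**3. All three must succeed.** All three tests can be significant only if the HbA1c test is, so error is not inflated. With no effect on any measure, the simulated chance of three favourable results is 0.4% at r = 0.7 and 0.7% at r = 0.8, well below 2.5%. For the same reason, power for the joint claim cannot exceed the power for HbA1c. How far below it lies cannot be computed, because the article gives no effect size or SD for the two glucose measures.

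**4. HbA1c alone decides.** The error rate is 5%, and the 90% power applies as stated.

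**5. The three readings side by side.**

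| Reading of the primary outcome | Stated 5% holds? | Stated 90% describes the primary claim? |
|---|---|---|
| Any one measure | No | No |
| All three | Yes, conservative | No |
| HbA1c decides | Yes | Yes |

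Only the last reading agrees with the sample size section, and the outcome definition does not state it.

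**The case against.** The case on the other side has several parts.

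- **An unseen document may settle it.** This is a condensed article, and a full protocol or SAP may contain a testing order or an adjustment. That stands for multiplicity procedures, whose absence here is no finding. It does not cover the choice of the deciding measure. That belongs to the outcome definition, which the article does give and leaves open.
- **HbA1c already leads.** It is the only glycaemic eligibility criterion (above 7.5%, under Study participants and inclusion criteria) and the only measure used for sizing. This makes a free choice among three equal measures a less natural reading, but it does not make HbA1c the sole primary outcome.
- **No inflated rule is written down.** A reader might infer that a win on one spot glucose counts as success under the plan, or that three separate primary tests at 0.05 are specified. Neither is stated. The text gives a general threshold and fails to exclude that use.
- **The size is conditional.** A reader might conclude that the error rate is about double the stated 5%. That needs both the any-one rule and correlations near 0.7 to 0.8, and the article supplies neither.
- **Power for the glucose measures is unknown.** A reader might say that the trial is underpowered for them. The documents support only that they were not used for sizing. Planned enrolment is 600, about 300 per arm, against a calculated 36 per group.

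**Conclusion.** The point holds as a defect in the outcome definition. Three measures are primary, none is named as deciding, and the stated 5% and 90% describe the primary claim under only one of the three possible readings.

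The inflation is conditional. It requires that any one significant measure counts and that each test holds its nominal 5%. On those terms the two-sided error is 14.3% at independence, 10.9% to 9.8% for r from 0.7 to 0.8, and 7.3% at 0.95, with all correlations assumed. No single multiple of 5% can be read from the document.

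These figures should not be added to any effect of allocating three centres to each group. If patient-level tests ignored that clustering, they would not hold their nominal 5%, and the figures above would no longer apply. That is a separate question, and nothing here measures it.

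Confidence is high that the rule is missing, and lower on how large the consequence would be. The change should be made.

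**What to change.** Name 12-month HbA1c, adjusted for baseline, as the single primary outcome, and move fasting and 2-hour postprandial glucose to the secondary outcomes. This brings the outcome definition into line with the sample size section and keeps the primary error rate at 5%, provided that the test itself is valid.

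If all three are to stay primary, state a fixed testing order with HbA1c first and the order of the other two given. Each measure is then tested at 0.05 only if the one before it succeeded, which also holds the overall rate at 5%.

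Data collection does not change, because Table 3 already schedules all three measures at baseline and at every follow-up visit. The sponsor gives up a primary claim based on spot glucose alone. The wording change is short, but it alters the primary outcome of a running trial: Trial status gives May 2021 as the start of recruitment. It therefore needs a dated amendment with its reason, made before outcome data are compared by group.

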#### Secondary outcomes measures

Secondary outcomes are the following measures adjusted for baseline values:patients’ medication adherence, diabetes knowledge and lifestyle;patients’ hospitalization or emergency room visits and incidence of complications related to diabetes;height, weight, waist to hip ratio, blood pressure and lipid files;costs on diabetes management.

### Data monitoring

#### Monitoring of study process

The study will be divided into several tasks, and each task is scheduled to be finished in a certain time. The process of each task will be monitored and evaluated according to the timeline. Periodically, an internet meeting consisting of the PI, main research staff, data collectors will be held, and a main research staff from the Second Xiangya Hospital will go to the primary hospitals to check the progress of the project regularly.

#### Quality control procedures

Serial tests will be carried out during the 3 months’ training time to ensure the trained pharmacists are able to provide qualified services in the collaborative clinics in the primary hospitals. The trained data collectors will follow standard procedures to enroll patients, collect data and upload electronic data. An electronic CRF form of each patient is required to be uploaded to the Second Xiangya Hospital within two days. A separate staff who are in charge of data collection and analysis will check the data’s validity and integrity.

### Data analyses

The sample size was calculated by using the PowerSampleSize program (Vanderbilt University). The data will be analyzed using the SPSS software package (Statistical Package for the Social Sciences), version 22.0 for Windows (SPSS Inc., Chicago, Illinois, USA). Data will be checked for normal distribution by means of the Kolmogorov–Smirnov's test. Values are presented as mean ± standard deviation or median (range) for parametrically or nonparametrically distributed variables, respectively. In compliance with the distribution of data, Student's t-test or Mann–Whitney's U-test will be used for comparisons between the two groups. Chi-square or Fisher's exact tests will be used to compare between the groups with respect to categorical data. The follow-up assessment data will be analyzed using Generalized Linear Mixed Model and survival analysis. *P* < 0.05 is considered statistically significant. All tests are two tailed.

For cost-effectiveness analysis, we will collect the direct and indirect costs of each enrolled patient with T2DM, evaluate their quality of life through EQ-5D-3L utility value from data provided by patients, calculate quality-adjusted life years (QALYs), and analyze the effects of multiple variables by the Linear Mixed Effects Model. Based on this model, the differences between the average costs and the results will be analyzed during the 12 months. The incremental cost effectiveness (ICER) will be calculated, and the univariate and multivariate analyses will be performed.

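### The outcomes are defined as baseline-adjusted, but the analysis section names both an unadjusted test chosen by a normality check and a mixed model for the 12-month data, and does not say which one gives the primary result

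*Protocol article*

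**What the plan says.** **Outcome definition.** Under Primary outcomes measure, the protocol article takes fasting glucose, 2-hour postprandial glucose and HbA1c "at 12 months’ follow-up adjusted for baseline value". Under Secondary outcomes measures it writes "Secondary outcomes are the following measures adjusted for baseline values".

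**Analysis.** The first paragraph of Data analyses contains these steps:

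- A normality check: "Data will be checked for normal distribution by means of the Kolmogorov–Smirnov's test".
- A summary that follows the check: "Values are presented as mean ± standard deviation or median (range) for parametrically or nonparametrically distributed variables, respectively".
- A test that follows the check: depending on the distribution, a t-test or a Mann–Whitney "U-test will be used for comparisons between the two groups".
- A model: "The follow-up assessment data will be analyzed using Generalized Linear Mixed Model and survival analysis".

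Nothing confines the t-test/Mann–Whitney sentence to baseline data. The mixed-model sentence does not mention the baseline value. The Covariates section lists what is measured, including HbA1c and both glucose values, but ties no variable to a model.

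**Size and allocation.** Sample size determination rests on a difference in mean HbA1c of 0.76 with SD 1.0. Randomization and allocation concealment places three centres in each group.

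**The concern.** The 12-month glucose outcome falls under two sentences of the same paragraph. It is a comparison between the two groups, so the t-test/Mann–Whitney rule applies. It is also follow-up assessment data, so the mixed model applies. Only the second route can meet the outcome definition, and the text does not choose between them.

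Two things are at stake. First, an unadjusted comparison carries part of any baseline difference between the arms into the estimated effect, and with few hospitals per arm such a difference is easier to get than with 600 individually randomised patients. Second, the normality check decides what is reported: a difference in means, which the trial was sized on, or a rank comparison with medians. Two analysts following the text could give different primary results from the same data.

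**Working it through.** **1. The plan's own figure.** Inputs from Sample size determination: difference 0.76, SD 1.0, two-sided α = 0.05, power 90%.

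n per group = 2 × [(1.960 + 1.282) × 1.0 / 0.76]² = 36.4

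The article states 36, so the figure reproduces to within rounding. It is the formula for an unadjusted difference of two means. The quantity sized for is therefore a mean difference, not a rank statistic.

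**2. Shift from a baseline difference.** If baseline and 12-month SDs are equal, an unadjusted comparison is shifted by about r×d. The article gives neither r nor d, so both are assumed. For d = 0.3 HbA1c points:

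| r (assumed) | shift r × 0.3 | share of 0.76 |
|---|---|---|
| 0.3 | 0.09 | 12% |
| 0.5 | 0.15 | 20% |
| 0.7 | 0.21 | 28% |

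**3. Is such an imbalance plausible?** With three hospitals of 100 patients per arm, the SD of the between-arm baseline difference, in units of the patient-level SD, is √{(2/3) × [ICC + (1 − ICC)/100]}.

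- ICC 0.01 (assumed): √(0.6667 × 0.0199) = 0.12
- ICC 0.05 (assumed): √(0.6667 × 0.0595) = 0.20
- Individual randomisation, 300 per arm: √(2/300) = 0.08

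Taking the SD of 1.0 for baseline as well, d = 0.3 is 0.3/0.199 = 1.5 of these SDs at ICC 0.05 and 0.3/0.115 = 2.6 at ICC 0.01. On a normal distribution, an absolute difference at least that large has a chance of about 13% and 1% respectively. So 0.3 is a large but realistic imbalance at the higher ICC and an unlikely one at the lower.

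**4. Effect on the test.** Simulation with 300 per arm, no treatment effect, r = 0.5, independent patients and 1,500 runs per row:

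| baseline imbalance (SD) | t-test rejects | ANCOVA rejects |
|---|---|---|
| 0 | 2% | 5% |
| 0.1 | 6% | 6% |
| 0.2 | 19% | 4% |
| 0.3 | 45% | 4% |

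These rates are conditional on the imbalance. They isolate the baseline problem and leave out clustering of follow-up values within hospitals. They do not show that ANCOVA without a hospital term would suffice.

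**5. How often the check would switch the test.** Simulated lognormal data, n = 300, 1,000 runs per row. The skewness values are assumed, since the article gives none:

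| skewness | plain K–S rejects | with Lilliefors correction |
|---|---|---|
| 0.3 | 0.5% | 18% |
| 0.6 | 10% | 65% |
| 1.1 | 74% | 99% |
| 1.75 | 99.5% | 100% |

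Gamma data with n = 270 to 300 give the same picture: at skewness 0.5, about 3 to 5% for the plain test and 45 to 52% with the correction. The article does not say which variant is meant, or whether the check is run per arm or pooled. The n of 300 assumes per arm.

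**The case against.** The strongest reply is that the paragraph already contains the right tool. The 12-month outcome is follow-up data, the mixed model is assigned to follow-up data, and it can carry the baseline value. On a natural reading the t-test, Mann–Whitney and chi-square sentences describe baseline or simple comparisons. The model's covariates and random effects are detail that a condensed article may leave to an analysis plan that is not shown.

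Much of this stands. A reader might infer that the trial plans only an unadjusted test; the mixed-model sentence rules that out. Nor is the missing covariate list a finding. What remains is that the t-test/Mann–Whitney rule is stated for group comparisons without restriction, conflicts with the outcome definition, and is not ranked against the model.

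Three other stronger readings also fail:

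- **Costs.** A reader might infer that mean costs would be compared by a rank test. The second paragraph of Data analyses assigns average costs to a linear mixed effects model.
- **Precision.** Adjustment removes r² of the patient-level variance: 25% at r = 0.5 and 49% at r = 0.7. But between-hospital variation makes up 0.01/0.0199 = 50% of the variance of the arm difference at ICC 0.01, and 0.05/0.0595 = 84% at ICC 0.05. Unless baseline also explains hospital differences, the total falls by only about 12%/24% or 4%/8%. With about 300 planned per arm against 36 calculated, lack of precision at patient level is not the argument.
- **Full carry-over.** A baseline difference does not pass into the estimate in full; only about r×d of it does.

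**Conclusion.** The point holds as an unresolved conflict within the protocol article. The outcomes are defined as baseline-adjusted. Two analyses apply to the 12-month values, one of which cannot adjust, and the text does not say which gives the primary result.

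If the unadjusted route were followed, the estimate would move by 0.09 to 0.21 HbA1c points for a baseline difference of 0.3 and r of 0.3 to 0.7. That is 12 to 28% of the design difference. The values of r, d and the ICC, and equal SDs at baseline and follow-up, are assumptions. The ICC calculation takes allocation to be by hospital, as the three-centres-per-group statement implies.

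That the normality check is a poor selection rule follows from the text alone, because it can replace the estimand used for sizing. How often it would do so here cannot be known: it depends on the skewness of the data and on the K–S variant. Whether HbA1c should be the sole primary outcome is a separate question and is not judged here.

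**What to change.** In the first paragraph of Data analyses:

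1. Delete the Kolmogorov–Smirnov-driven choice of test for outcome comparisons.
2. Limit the t-test and Mann–Whitney test to baseline or descriptive tables.
3. State that each 12-month glucose outcome is analysed by the mixed model already planned, reporting an adjusted mean difference at 12 months, with the baseline value of that outcome as covariate and hospital as a random effect.
4. Add a small-sample degrees-of-freedom correction for six hospitals. Without one, a mixed model with so few hospitals can itself reject too often.

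**Cost.** This changes wording only; Table 3 already schedules the baseline measurements. It takes slightly more analysis work. Intervals will be wider once hospital is modelled: a comparison made between hospitals has about 6 − 2 = 4 degrees of freedom, where the two-sided 5% critical value is 2.78 rather than 1.96. That width reflects allocation by hospital, which the simple tests would ignore.

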#### Baseline interview

Baseline investigations will be carried out in all the participated six primary hospitals. The contents of the investigations include four aspects, namely socio-demographic parameters, clinical parameters, process indicators and costs on diabetes as shown in Table 2. Data collectors are responsible to guide enrolled patients to finish the baseline investigations. The information of body weight, height, waistline and blood pressure will be measured and recorded in the clinic by the data collector. The Glucose and lipid files will be measured by lab tests. Data of patient socio-demographic parameters, process indicators and costs on diabetes will be provided by the patients or their guardians.

**Table 2 Tab2:** Services to be provided by pharmacists in the primary hospitals

Pharmacists’ services	Details	Methods
Diabetes education	□ Disease introduction □ Control target of blood glucose □ The types and principles of hypoglycemic agents □ Self-monitoring of blood glucose	□ Educate patients of diabetes management in the collaborative clinic. The knowledge will be printed out and given to patients for home study
Medication guidance	□ The importance of medication adherence □ Administration methods(oral & injection medication) □ Administration timing □ The injection technique of insulin □ Drug-drug interaction □ Drug storage	□ Create a WeChat group with all the enrolled patients in, and pharmacists will share diabetes knowledge periodically
Lifestyle intervention	□ Exercise □ Diet	□ Educate patients in the collaborative clinic □ Help patients make a healthy lifestyle plan
ADR * & complications identification and treatment	□ Recognition and prevention of hypoglycemia □ Identification and processing of complications of diabetes □ Identification and processing of ADR	□ Educate patients in the collaborative clinic □ Call the pharmacist if an emergency event occurs

*PS*: *ADR* Adverse drug reaction

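### The planned QALYs and ICER depend on EQ-5D-3L utilities that the article's collection schedule places at no time-point

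*Protocol article*

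**What the plan says.** The Data analyses section of the Protocol article says that the economic evaluation will "evaluate their quality of life through EQ-5D-3L utility value from data provided by patients, calculate quality-adjusted life years (QALYs". On the horizon it says that "the differences between the average costs and the results will be analyzed during the 12 months", and on the ratio that "The incremental cost effectiveness (ICER) will be calculated, and the univariate and multivariate analyses will be performed". The Methods part of the Abstract names cost-effectiveness, next to effectiveness, as what the trial is to evaluate.

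The section on follow-up visits and data collection fixes what is gathered and when: "The measurement domains required to collect, survey methods and collection time-points are listed in Table 3". For the baseline interview the article states: "The contents of the investigations include four aspects, namely socio-demographic parameters, clinical parameters, process indicators and costs on diabetes". The Covariates section repeats these four aspects with their items. The secondary outcomes include costs, and also hospitalisation or emergency room visits.

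**The concern.** A QALY is the area under a patient's utility values over time. It needs a utility at the start and at one or more later points. The article names the instrument and the quantities to be derived from it, but the instrument is missing from the table it presents as its collection schedule. A data collector who follows that table would ask about costs at every visit and never administer EQ-5D-3L.

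Two things are at stake. The first is a stated aim of the trial: without utilities the ICER has a numerator (costs) but no QALY denominator. The second is baseline comparability. The section on randomization and allocation concealment places three centres in each group, so differences between a few hospitals can become differences between arms. A baseline utility is needed to detect and adjust for such a difference, and it cannot be obtained later.

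**Working it through.** The plan gives no figure to reproduce here. The check compares each listing of collected data with what the analysis needs.

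| Place in the Protocol article | Content | EQ-5D-3L or quality-of-life items |
|---|---|---|
| Baseline interview | Four aspects: socio-demographic, clinical, process, costs | 0 |
| Table 3, clinical row | Anthropometry, glucose measures, complications, blood pressure, lipids | 0 |
| Table 3, behavior rows | "Medication adherence, diabetes’ knowledge, lifestyle, diabetes treatment target and treatment behavior"; also "Treatment satisfaction" at month 12 | 0 |
| Table 3, economic row | Direct and indirect costs, at all five time-points | 0 |
| Primary and secondary outcomes | Glucose control; adherence, knowledge and lifestyle; events; physical measures and lipids; costs | 0 |
| Covariates | The same four aspects, itemised | 0 |
| Data analyses | EQ-5D-3L utilities, QALYs, ICER | Required |

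Lifestyle, treatment behavior and treatment satisfaction are not health utilities and cannot replace EQ-5D-3L.

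**Utilities a 12-month QALY needs.** Take the visits in Table 3 (baseline and months 3, 6, 9, 12) at times 0, 0.25, 0.5, 0.75 and 1 year, with U the utility at each. By the trapezoid rule:

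- QALY = 0.125·U0 + 0.25·U3 + 0.25·U6 + 0.25·U9 + 0.125·U12.
- The weights sum to 0.125 + 0.25 + 0.25 + 0.25 + 0.125 = 1.0 year.
- With baseline and month 12 only, QALY = 0.5·U0 + 0.5·U12. This is the minimum for a 12-month area.

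Table 3 as printed schedules none of the five utilities. U0 enters both formulas.

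**Why baseline utility matters.** Suppose the arms differ in utility by d at baseline and the gap persists all year. The unadjusted QALY difference then contains d × 1.0 = d. The documents give no value for d. For an assumed d of 0.02 to 0.05, the spurious part is 0.02 to 0.05 QALYs. The article states no expected QALY difference to set against this.

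**Timing.** The Trial status section says recruitment began in May 2021. The sample size section plans six months of recruitment plus at most one more. The article was published in March 2022. If all hospitals kept to that plan, enrolment was over by publication, and any baseline utility not taken by then is lost.

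**Emergency room visits.** These are part of a secondary outcome, but Table 3 has no item for them. Hospitalisation appears there only as a fee.

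**The case against.** The strongest reply is that the article itself says the utilities come from patients, so collection is intended, and that the CRF, which is not shown, may carry the questionnaire. Table 3 also works at the level of domains. It names no instrument for adherence, knowledge or satisfaction, and it gives interview methods for laboratory values that the Baseline interview section says come from lab tests. In the text available, the behavior row has an empty method cell and doubled ticks, so a cell-by-cell reading deserves caution. A journal article may leave such detail to the full protocol.

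Much of this stands, and it limits the point. A reader might infer that the QALY analysis cannot be done, or that QALYs will be missing for all of the roughly 600 patients. The documents do not support that: it would require Table 3 to be exhaustive and to override the analysis section. A reader might also fear that EQ-5D-3L would be taken only at the end, giving an ICER confounded by baseline differences. No section says so, and the planned linear mixed effects model over 12 months fits repeated measurement better.

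The reply does not remove the contradiction. The allowance for a condensed article covers silence. Here the article prints what it calls the required domains with their time-points, then plans an analysis on a variable absent from that list and from three others.

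**Conclusion.** The point holds as an inconsistency between the collection schedule and the planned analysis. EQ-5D-3L appears in the analysis section and in none of the four listings of what is measured (baseline interview, Table 3, outcomes, Covariates). Costs are supported at five of five time-points and utilities at none, so only the QALY side of the ICER is affected. The cost analysis and the primary glycaemic comparison stand.

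The conclusion assumes that Table 3, as extracted, has lost no row, and that sites work from it. If the CRF already contains EQ-5D-3L at suitable visits, this is a reporting error and one row corrects it. If it does not, a stated aim has no utility data, and the baseline part cannot be recovered for patients already enrolled. The documents do not show which is the case. The 0.02 to 0.05 QALY illustration rests on an assumed, persistent baseline gap and is not an estimate for this trial.

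**What to change.** Reconcile the sections as follows.

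- Add EQ-5D-3L to the baseline interview and to Table 3, at baseline and at follow-up visits that already take place: at least month 12, preferably months 3, 6, 9 and 12.
- List utility and QALYs among the secondary outcomes.
- State that QALYs are computed by area under the curve and compared with adjustment for baseline utility. With three hospitals per arm, baseline differences between arms are likely.
- If patients were enrolled without a baseline EQ-5D-3L, report how many and name it as a limitation of the QALY analysis. The contradiction does not by itself require a different main ICER, for example cost per unit of HbA1c; that would be a matter of preference.
- Separately, add a count of emergency room visits to Table 3, so that the named secondary outcome has a data source.

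The cost is a short questionnaire and one count question at existing visits, plus a CRF amendment if they are not already on the form.
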